**Fig. 4 Fig4:**
[figure not shown]
Objective quantification of exercise adherence for a full exercise session comprising three sets of 12 repetitions

**Fig. 5 Fig5:**
[figure not shown]
Objective quantification of exercise adherence for a single exercise set of 12 repetitions

##### Adverse events

All adverse events occurring while the patients are enrolled in the trial will be recorded regardless of their relation to the exercise intervention, surgery or occurrence likely not related to the trial. Thus, an adverse event can both be a negative effect of the intervention, surgery or an occurrence not related to the trial, that is an untoward occurrence during the trial which may or may not causally related to the intervention or trial. Regardless of a relation to the trial, all adverse events are recorded and reported.

Finally, a qualitative study will be embedded in the trial. Semi-structured interviews will be performed with randomly selected participating patients both before and after the trial about their experienced enablers and barriers related to the knee-extensor strength exercise and adherence to the home-based intervention. The orthopedic surgeons allocated to the trial will also undergo semi-structured interviews about their experienced enablers and barriers with the non-surgical, pre-operative, home-based intervention both before and after the trial. The physiotherapists allocated to the trial will undergo focus interviews, both before the trial is commenced and once the trial is completed, to explore their experienced enablers and barriers related to administering the home-based intervention. This embedded qualitative study is undertaken to refine the home-based intervention for future trials and clinical implementation. This knowledge can then be used to design a context-specific implementation plan, given a positive trial outcome. The embedded qualitative study will be reported in a separate qualitative paper, with a clear reference to the QUADX-1 trial.

Regular auditing is planned during the trial. Regular meetings between the primary investigator, the orthopedic department, the municipalities and the research team will allow for checking of treatment notes and outcome assessment forms for fidelity to protocol which allows for addressing deviations.

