### Recruitment

All patients will be included by consecutive sampling from the orthopedic outpatient clinic at Copenhagen University Hospital, Hvidovre. At the orthopedic outpatient clinic, possible patients for TKA surgery due to end-stage knee OA are introduced to the trial and offered to participate by the orthopedic surgeon if they fit the initial eligibility criteria (please see below). On the same day, eligible patients interested in participating in the trial are then referred to a research assistant who provides thorough oral and written information about the trial. Eligible patients are informed that participation in the project includes 12 weeks of home-based, knee-extensor strength exercise with the purpose of improving knee-extensor strength, relieving knee pain and improving functional performance. Further, they are informed that after the exercise period, they will be re-assessed at the orthopedic outpatient clinic with regards to undergo surgery or not. To prevent performance bias, eligible patients are blinded to the exercise dosage randomization as well as the trial hypothesis. Information about the trial is provided in a calm setting dedicated to the trial. Should the patients wish for a companion to be present during the information meeting a new information appointment is scheduled. Along with the information, a second more thorough screening of inclusion and exclusion criteria is commenced. The patients are given a minimum of 24 h to decide whether they would like to participate in the trial or not. If the patients decide to participate, a baseline assessment is scheduled. Written informed consent is obtained at the baseline assessment. Once written informed consent and baseline assessment is completed, the patient is fully included in the trial. Outcome assessments will be performed blinded by the primary investigator and a research assistant dedicated to the trial, who are both trained according to the trial outcome-assessment protocol to ensure standardized assessments throughout the trial. To further refine and ensure standardization of the trial outcome-assessment protocol we piloted the outcome-assessment procedures in seven patients prior to initiating the trial.

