### Elaborated description of outcome measures

#### Primary outcome

##### Isometric knee-extensor strength

The measurement will be assessed using a computerized strength chair (Good Strength Chair, Metitur Oy, Jyvaskyla, Finland). This is a valid (0.78–0.92) and reliable (inter-trial 0.98–1.00 (standard error of measurement (SEM) < 10%), inter-evaluator 0.92–0.99 (SEM 8.34–9.92%)) knee-extensor strength measure in the TKA population [35].

Prior to outcome assessment, the patients will be informed about the procedure. The measurement consists of five maximal isometric knee-extensor contractions at 60° knee flexion separated by a 60-s pauses. The highest obtained value will be used for analysis. The patients are instructed to extend their knee as forcefully as possible with a gradual increase in force over a 5-s period. There will be strong and standardized verbal encouragement during each contraction. Knee-extensor strength will subsequently be expressed as the maximal voluntary torque per kilogram body mass (Nm/kg) using the external lever arm and body mass of each patient. Results will be presented, firstly, as absolute changes (Nm/kg) and, secondly, as relative changes (%) from baseline.

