### Randomization

The patients will be randomly assigned to one of the three intervention groups (two, four or six sessions per week) by a 1:1:1 allocation ratio. The generation of the allocation sequence will be attended to by a statistician not involved in the trial in any other way. One hundred and forty opaque and sealed envelopes will be generated. After being included in the trial (signed written informed consent and completion of baseline assessment) a person independent of the trial will open one of these envelopes and inform the patient’s municipality which of the three exercise groups the patient is allocated to. In this way, the allocation information is kept secret from the outcome assessor.

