### Blinding

The primary investigator collecting the outcomes (outcome assessor) as well as the data analysts will be blinded to allocation. At outcome assessment sessions, the outcome assessor will start by informing the patients that they are not allowed to mention what exercise dosage they have received. The data will be coded in such a way that group allocation is concealed in the dataset, thus blinding the outcome assessors and data analysts to the group allocation. The patients and the physiotherapists instructing in the intervention will not be blinded due to the nature of the intervention; however, the patients will be blinded to the exercise dosages in the other groups, which exercise dosages will be compared in the analysis and which dosage is hypothesized to have the largest effect. Unblinding will only happen in the case where the wellbeing a the patient is at risk. This will be assessed in collaboration with the patient’s physician.

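### The blinded outcome assessor attends audit meetings with the municipalities at which treatment notes are checked, and nothing stated keeps the exercise dosage out of those meetings

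*Protocol article*

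**What the plan says.** Four parts of the protocol article bear on this.

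- **Randomization.** A person independent of the trial opens the envelope and will "inform the patient’s municipality which of the three exercise groups the patient is allocated to". The section concludes that this keeps allocation secret from the assessor. The municipality is the only party it names as being told.
- **Blinding.** "The primary investigator collecting the outcomes (outcome assessor) as well as the data analysts will be blinded to allocation". The same section says that "the physiotherapists instructing in the intervention will not be blinded due to the nature of the intervention". Its safeguards are that patients are told not to mention their dosage at assessments, that group is coded in the dataset, and that unblinding is limited to cases where a patient's wellbeing is at risk.
- **Recruitment.** There are two assessors: "Outcome assessments will be performed blinded by the primary investigator and a research assistant dedicated to the trial".
- **Adverse events, closing paragraph.** "Regular auditing is planned during the trial". It continues: "Regular meetings between the primary investigator, the orthopedic department, the municipalities and the research team will allow for checking of treatment notes", together with outcome assessment forms, to verify fidelity to the protocol and deal with deviations.

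The section on isometric knee-extensor strength describes the primary outcome as the best of five maximal contractions in a computerized chair, and adds: "There will be strong and standardized verbal encouragement during each contraction".

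**The concern.** Concealment from the assessor depends on keeping the knowledge of dosage in the municipality. The audit paragraph brings the assessor together with the municipality, repeatedly and while patients are still to be assessed, to go over records of the treatment. If dosage comes up there, the assessor may know a patient's arm when running the strength test.

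Detection bias in the primary contrast is at stake. The outcome depends on the patient's effort and on the assessor's coaching. The Hypothesis section expects four sessions per week to give the greatest pre-operative gain, and the article hides that hypothesis from patients to limit bias. With no control group, every conclusion rests on contrasts between dosages, so anything that treats one dosage group differently at testing acts directly on the result.

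**Working it through.** The protocol gives no figure on this point, so no arithmetic applies. The check is whether the passages can all be carried out as written.

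1. **Who must not know.** The primary investigator and the research assistant (Recruitment, Blinding).
2. **Who knows.** The municipality, told at randomization, and its unblinded physiotherapists (Randomization, Blinding).
3. **Where they meet.** The audit meetings list the primary investigator and the municipalities as participants (Adverse events). The research assistant is not named but could fall within the research team, which is also listed.
4. **When.** Auditing takes place during the trial. A patient's instruction and the check-ups at 4 and 8 weeks happen at the municipality (Intervention). The primary endpoint follows the 12-week period. Notes on a patient can therefore exist, and be discussed, before that patient's primary assessment. The same holds for the later assessments at discharge and 3 months after surgery.
5. **What could be revealed.** In Tables 1 and 2 the load, sets, repetitions and duration are the same in all groups. The groups differ only in sessions per week and the recovery days that follow from it. Fidelity to the allocated dosage cannot be checked without knowing that dosage.
6. **Whether a stated safeguard closes the route.** The instruction to patients covers the assessment visit. Coding covers the dataset. The limit on unblinding covers deliberate disclosure. None deals with notes or meetings, and the article does not say that notes are redacted or that assessors leave while they are checked.
7. **Whether knowledge could affect the outcome.** The test is a maximal voluntary effort with encouragement. Standardized wording, a computerized chair and taking the best of five values narrow the room for influence but do not remove it.

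Steps 1 to 4 and 6 rest on the text. Step 5 is an inference about what the notes contain, and step 7 is a judgment about susceptibility.

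**The case against.** The strongest reply is that the leak is inferred. The article speaks of treatment notes without saying whose they are, that they show dosage, or that the primary investigator reads them. It says that the meetings allow checking, not who checks what. The listed content of the check-ups is technique, band resistance and patients' questions, none of which need show session frequency. The blinding rule is stated without exception, so the audit paragraph can be read as subject to it. A condensed article may also leave masking procedures for meetings to the full protocol.

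Much of this stands. A reader might infer that the assessor will be unblinded, or that the claim of blinding is false. The document supports neither; it supports only that the arm can be revealed. What does not fall away is the conflict in the text itself. One section relies on separating the assessor from the municipality, and another brings them together over treatment records. That is something stated, not merely a missing detail.

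Two further inferences should be resisted. A reader might attach an inflated false-positive rate to this. Any such figure needs an assumed assessor-induced shift, for which the document gives no basis, and it would require the assessors to learn and act on the dosage of many patients. A reader might also argue that sensor session counts would unblind the analysts. The article describes no step that merges those data before the primary analysis, and the order of data release is ordinary content of a statistical analysis plan.

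**Conclusion.** The point holds as a conflict between sections that leaves a plausible route to unblinding of the outcome assessor before the primary endpoint. It rests on one inference: that notes or discussions about fidelity, with a municipality that knows each patient's group, can disclose sessions per week. The size of any bias cannot be estimated from the document, and standardized encouragement and a computerized measurement limit it. No stated figure, including the sample size, changes. The correction is worth making because it protects the only contrast on which the primary conclusion depends and costs little. It does not imply that unblinding has occurred.

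**What to change.** Amend the audit paragraph under Adverse events and cross-refer to it in Blinding, so that:

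- treatment notes and fidelity to the allocated dosage are checked by existing trial or municipality staff who do not assess outcomes, or on notes from which the dosage has been removed;
- both outcome assessors, the primary investigator and the research assistant, see only outcome forms and de-identified issues without dosage until the last outcome assessment.

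The sponsor should confirm that whoever takes over the check is not an assessor. The trial manager is an obvious candidate, but the article says only that this person is a physiotherapist, and it describes the outcome assessor as a physiotherapist too. It does not establish that they are different people.

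The cost is reassigning an existing task or redacting the notes. The downside is that the primary investigator loses direct oversight of the unredacted treatment notes and must rely on another person's report of deviations.

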### Sample size

For a three-group-level One-way ANOVA of a normal mean difference with a two-sided significance level of 0.05, a common standard deviation of 0.22 Nm/kg (isometric knee-extensor strength measurement) [51], and a minimal clinically important difference of 0.15 Nm/kg (15%), a sample size of 126 (42 per group) patients is required to obtain a power of 80%. To allow for a dropout rate of 10%, we will include 140 patients in total for the intention-to-treat (ITT) analysis (3 × 42 + 14 = 140).

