#### Primary outcome

Change in isometric knee-extensor strength from baseline (week 0) to after the intervention period (> 12 weeks). Knee-extensor strength is chosen as the primary outcome for the following reasons. Firstly, it is an outcome closely related to the exposure (strength training), which we consider important in a dose-response trial, because other health effects are likely mediated via increased knee-extensor strength. Secondly, knee-extensor strength is associated with the development and progression of knee OA and knee pain and function [9, 10], and as such, we also consider the outcome, a surrogate measure for the development and progression of knee OA, knee pain and function.

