### Statistical analysis

#### Analysis outline

Three groups; group 2 = two sessions/week, group 4 = four sessions/week and group 6 = six sessions/week. There is no control group. The primary outcome is the change in isometric knee-extensor strength. Time from baseline to after 12 weeks of exercise is the primary endpoint (Δ_t0-t1_) and time from baseline to just before hospital discharge, and time from baseline to 3 months after surgery are the secondary endpoints (Δ_t0-t2_ and Δ_t0-t3_, respectively). The analysis plans for the primary and secondary analyses are outlined in Table 3.

**Table 3 Tab3:** Analysis outline for primary and secondary analysis

Variable/outcome	Hypothesis	Outcome measure (unit, scale)	Methods of analysis
Descriptive statistics (sample characteristics)		Age, weight, height, side of index knee (continuous and dichotomous)	Summary statistics
Primary analysis			
Primary outcome			
1. Change in *isometric knee-extensor strength* Δ_t0-t1_	Group 2 < Group 4 Group 4 ≈ Group 6	Change in Nm/kg (continuous)	Analysis of variance ANOVA^a^
Secondary analysis			
Secondary outcomes			
2. Change in *isometric knee-extensor strength* Δ_t0-t2_, Δ_t0-t3_	Group 2 < Group 4 Group 4 ≈ Group 6	Change in Nm/kg (continuous)	ANOVA^a^
3. Change in *Knee Osteoarthritis Outcome Score* (KOOS) subscales Δ_t0-t1_, Δ_t0-t3_	Group 2 < Group 4 Group 4 > Group 6	Change in questionnaire subscales (continuous)	ANOVA^a^
4. Change in *Oxford Knee Score* (OKS) Δ_t0-t1_, Δ_t0-t3_	Group 2 < Group 4 Group 4 > Group 6	Change in questionnaire (continuous)	ANOVA^a^
5. Change in *6-Minute Walking Test for distance* (6MWT) Δ_t0-t1_, Δ_t0-t2_, Δ_t0-t3_	Group 2 < Group 4 Group 4 > Group 6	Change in meters walked (continuous)	ANOVA^a^
6. Change in *Stair Climb Test* (SCT) Δ_t0-t1_, Δ_t0-t2_, Δ_t0-t3_	Group 2 < Group 4 Group 4 > Group 6	Change in time used to ascend and descend stairs (continuous)	ANOVA^a^
7. Change in *current knee pain* (Numeric Rank Scale, NRS) Δ_t0-t1_, Δ_t0-t2_, Δ_t0-t3_	Group 2 < Group 4 Group 4 > Group 6	Change in NRS 0–10 (continuous)	ANOVA^a^
8. Change in *knee pain during the last week* (Numeric Rank Scale, NRS) Δ_t0-t1_, Δ_t0-t3_	Group 2 < Group 4 Group 4 > Group 6	Change in NRS 0–10 (continuous)	ANOVA^a^
9 Distribution in *need for surgery*	Group 2 < Group 4 Group 4 > Group 6	Yes, don’t know, no	Summary statistics
Other outcomes			

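### The sample size uses an SD labelled as that of the strength measurement, but the primary test is an unadjusted ANOVA of the change. The stated power therefore rests on an unstated correlation, which adjusting for baseline would largely remove.

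*Protocol article*

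**What the plan says.** All references are to the protocol article.

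- **Sample size.** The planned test is described in these words: "For a three-group-level One-way ANOVA of a normal mean difference". For the variability, the section takes "a common standard deviation of 0.22 Nm/kg (isometric knee-extensor strength measurement" from a cited source. Alpha is 0.05, two-sided, and the smallest difference of clinical interest is put at 0.15 Nm/kg, which the section equates with 15%. The result reads "a sample size of 126 (42 per group) patients is required to obtain a power of 80" per cent. The total is then raised to 140 to cover 10% dropout.
- **Primary outcome (under Outcomes).** "Change in isometric knee-extensor strength from baseline (week 0) to after the intervention period".
- **Analysis outline.** "The primary outcome is the change in isometric knee-extensor strength". Table 3 row 1 gives the measure as change in Nm/kg and the method as ANOVA, with Kruskal-Wallis if the data are not normal. It names no baseline covariate.
- **Isometric knee-extensor strength (elaborated description).** The only correlation-type figures for the measure are validity and reliability coefficients, such as 0.92–0.99 between evaluators. No baseline to 12-week correlation appears anywhere.

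**The concern.** The SD is labelled for one quantity and the test is run on another. A change score has the same SD as a single measurement only when the two occasions correlate at exactly 0.5 and have equal SDs. With a lower correlation the change is more variable and power falls below the stated value. With a higher one the trial has more power than stated. The article fixes the SD, the endpoint, the test and the power, but not the quantity that links them. As written, a reader cannot tell whether 80% describes the planned test.

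The choice of test also matters. Patients exercise at home for 12 weeks between the two measurements, and varied response to training would lower the correlation. An unadjusted change score is exposed to that. An analysis that adjusts for baseline strength is much less so, and baseline strength is measured in every patient before randomisation.

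**Working it through.** **Inputs from the article.** Three groups, 1:1:1, two-sided alpha 0.05, SD 0.22 Nm/kg, largest difference 0.15 Nm/kg, 42 per group (126 in all), 140 after 10% dropout.

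**Inputs that are assumptions.** The correlation r between baseline and 12 weeks is not given, so a range is shown. Unless stated otherwise, the SD is 0.22 at both times.

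**Step 1: reproduce the stated figure.** The power of the overall F test follows from a noncentral F distribution with 2 and 3n − 3 degrees of freedom and noncentrality λ = n Σ(μᵢ − μ̄)² / SD². With means 0, 0.075 and 0.15, Σ(μᵢ − μ̄)² = 2 × 0.075² = 0.01125. At n = 42, λ = 42 × 0.01125 / 0.0484 = 9.76 and power is 79.5%; the smallest n reaching 80% is 43. This matches 42 per group within rounding, so 0.22 was evidently entered directly as the SD of the analysed variable. The dropout step also holds: 126 / 0.9 = 140.

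**Step 2: what a single-occasion SD implies.**

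- SD of the change = 0.22 × √(2(1 − r)).
- Residual SD with baseline as covariate = 0.22 × √(1 − r²).

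Power at 42 per group, means 0, 0.075, 0.15:

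| r | SD of change | Power, ANOVA of change | Residual SD, ANCOVA | Power, ANCOVA |
|---|---|---|---|---|
| 0 | 0.311 | 48% | 0.220 | 79.5% |
| 0.3 | 0.260 | 64% | 0.210 | 83% |
| 0.4 | 0.241 | 71% | 0.202 | 86% |
| 0.5 | 0.220 | 79.5% | 0.191 | 90% |
| 0.6 | 0.197 | 88% | 0.176 | 94% |
| 0.7 | 0.170 | 96% | 0.157 | 98% |

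The covariate's one degree of freedom (122 instead of 123 for error) does not change these figures at the precision shown.

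**Step 3: the threshold.** Exactly 80% power at 42 per group needs an SD of at most 0.2188, so r ≥ 1 − 0.2188² / (2 × 0.22²) = 0.506, or about 0.5.

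**Step 4: how far the threshold depends on the pattern of means.** Table 3 expects Group 2 below Group 4, with Groups 4 and 6 about equal. With means 0, 0.15, 0.15, Σ(μᵢ − μ̄)² = 0.015, the largest SD compatible with 80% is 0.2526, and r need only be about 0.34. The change-score ANOVA then has 77% power at r = 0.3, 84% at 0.4 and 90% at 0.5. For a single pairwise contrast of 0.15, the threshold is about 0.38 without adjustment and about 0.53 at alpha 0.05/3.

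**Step 5: if the SD rises at 12 weeks.** Assume a baseline SD of 0.22, a measurement error SD of 0.09 and an independent training response with SD 0.20. The 12-week variance is 0.0484 + 0.0400 = 0.0884 (SD 0.297). The covariance is 0.0484 − 0.0081 = 0.0403, so r = 0.0403 / (0.22 × 0.297) = 0.62. The SD of the change is √(0.0484 + 0.0884 − 0.0806) = 0.237 and the ANCOVA residual SD is √(0.0884 − 0.0403² / 0.0484) = 0.234. Power is 73% and 74%. In this case r exceeds 0.5, both analyses fall short of 80%, and ANCOVA gains little.

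**The case against.** The strongest objection is that the premise rests on a label. The 0.22 comes from a cited source that is not at hand. The parenthesis may only name the instrument, and the calculation's opening words about a normal mean difference can be read either way. If 0.22 is the SD of a change, the stated power is right and only the label needs tidying. The article's reliability figures give a weak hint in that direction. If the mean is about 1.0 Nm/kg (an inference from 0.15 being called 15%), a standard error of measurement of 8.34% with reliability of at least 0.92 implies a single-occasion SD of at least 0.0834 / √0.08 = 0.29, above 0.22. The populations may differ, so this settles nothing. The objection stands to this extent: a shortfall cannot be claimed.

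Second, r above 0.5 is plausible for so reliable a measure, and the sample would then be larger than needed. On the same assumed mean, measurement error alone gives a change SD of only about 0.12 to 0.14. To reach 0.22, true changes would have to vary between patients with an SD of about 0.17 to 0.19, more than the 0.15 taken as clinically important. That is fair, but inter-evaluator reliability is not a correlation across 12 weeks of unsupervised training, and the article states no such correlation.

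Third, ANOVA of change is unbiased in a randomised trial and matches the defined outcome. That also stands. The case for the covariate is precision and adjustment for chance imbalance in baseline strength, not validity.

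**Conclusion.** The mismatch between the labelled SD and the analysed quantity is real. Its consequence is conditional. It matters if 0.22 is a single-occasion SD; given that, with equal SDs at both times and the midway pattern, 80% power needs r of about 0.5 or more, and under the pattern in Table 3 about 0.34.

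A reader might infer that the trial is underpowered. The document does not support that: the nature of 0.22 is unresolved, r is unknown, and above the threshold the trial has more power than stated. A reader might also infer that baseline adjustment secures 80% whatever happens. It does so, to within rounding, only if the SD does not rise at 12 weeks; Step 5 shows a case where it does not. What holds generally is narrower: the ANCOVA residual variance is never larger than the variance of the change, so adjustment costs at most one degree of freedom under either reading of 0.22. The point is a clarification together with an almost cost-free gain in precision, and it gives no reason to change the sample size.

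**What to change.** 1. **Sample size section.** Say whether 0.22 Nm/kg is the SD of one measurement or of the 12-week change. If it is the former, give the assumed correlation. State the power for the analysis that will be run.
2. **Table 3, row 1.** Replace the unadjusted ANOVA of change by ANCOVA of 12-week strength (or, equivalently for the group contrasts, of the change) on arm, with baseline strength as covariate.

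The cost is wording in the protocol and analysis plan and one degree of freedom. No new data and no change in the number of patients are needed, because baseline strength is already measured in everyone before allocation.
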